### Process

#### Preintervention Phase

Initially, current stroke management practices at selected health care facilities are assessed to estimate their preparedness, including infrastructure, equipment, human resources, diagnostics, laboratories, and radiological investigations. Available drugs along with a gap analysis shall also be reviewed while assessing preparedness. A scoring system shall be developed based on preintervention inputs weighted by their importance in improving survival, reducing disability, and enhancing QoL. Specific indicators will be created from this scoring system to assess preparedness and management practices.

#### The CASCADE: Development, Implementation, and Assessment of Effectiveness

The intervention is the CASCADE, which will be developed through a process of observation and expert consultation. The CASCADE intervention is a structured, multicomponent health care facility–based intervention tailored to each participating facility based on findings from the hospital preparedness assessment and gap analysis. While site-specific modifications may differ according to identified gaps, the overall intervention framework will remain uniform across all participating health care facilities. The detailed intervention package will be developed using evidence generated from the preintervention stroke data, hospital preparedness assessments, Indian stroke management guidelines, and recommendations from an expert panel that will validate and standardize the protocols and algorithms across different levels of care. The proposed CASCADE will include procedures and standards for screening, triaging, and management of stroke cases at different levels of health care, algorithm-driven management, and referral of stroke cases. The effectiveness or outcomes of the CASCADE being assessed are stroke survival, disability, and QoL over a period of 1 year after the stroke.

Once developed, the CASCADE will be implemented across study units. Health care facilities will be informed about their preparedness, management practices, and needed improvements based on preimplementation scores and indicators. Suggested modifications and personnel training will be provided. Training attendance, supportive supervision, and adherence to standardized protocols and algorithms will additionally be monitored during implementation. Implementation fidelity will be assessed using both facility-level and patient-level indicators. Preintervention and postintervention hospital preparedness assessments using standardized tools will evaluate changes in infrastructure, service availability, referral mechanisms, and stroke preparedness processes. The same indicators and scoring system will be used after the intervention to compare and estimate effectiveness of the CASCADE on outcomes of stroke care in the study unit. Figure 1 provides a schematic representation of development and implementation of the CASCADE.

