#### Hospital Preparedness

Observation of facilities, record review, and interviewing the personnel in charge of the health care facility (key informant interviews) will be recorded.

Trained data collectors collect data using a low-literacy, user-friendly digital data collection platform. These data get uploaded into a password-protected (3 layers) server with access only to specific authorized individuals within the study team.

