### Outcome Assessment

Increased survival, reduced disability, and improvement in stroke-specific QoL after introducing the CASCADE compared to the preintervention phase is considered an outcome. An increase in the scores and indicators of hospital preparedness and management practices is considered as the outcome for hospital preparedness.

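### A rise in the hospital preparedness score mainly shows that CASCADE was taken up, yet the Statistical Analysis section counts it in the primary effectiveness outcome, contradicting two other statements in the protocol

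*Protocol article*

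**What the plan says.** All references are to the protocol article.

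- **How the score is made.** Preintervention Phase: "A scoring system shall be developed based on preintervention inputs weighted by their importance in improving survival"; the sentence continues with disability and QoL. A gap analysis is part of the same assessment, and the indicators are derived from the score.
- **How it shapes the intervention.** The CASCADE section says the package is "tailored to each participating facility based on findings from the hospital preparedness assessment and gap analysis". Later in that section: "Health care facilities will be informed about their preparedness, management practices, and needed improvements based on preimplementation scores and indicators". Suggested modifications and staff training follow.
- **How it is reused.** Same section: "The same indicators and scoring system will be used after the intervention to compare and estimate effectiveness of the CASCADE".
- **How it is measured.** The Hospital Preparedness part of Data Collection combines observation of the facility, record review and "interviewing the personnel in charge of the health care facility (key informant interviews) will be recorded". Table 1 gives one assessment before and one after implementation.
- **What counts as the outcome.** Outcome Assessment: "An increase in the scores and indicators of hospital preparedness and management practices is considered as the outcome for hospital preparedness". No minimum size is given.
- **What status it has.** Statistical Analysis puts improved hospital preparedness, next to death, disability and QoL, in the primary outcome for CASCADE effectiveness. Sample Size names 28-day survival as the primary patient-level outcome and lists preparedness indicators among the secondary ones. The CASCADE section, before it describes implementation, defines the effectiveness being assessed as survival, disability and QoL over one year.

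**The concern.** Hospitals are told where they score low, are helped to correct it, and are then rescored with the same instrument. A higher second score is what delivery of the intervention looks like. It would be seen whether or not the corrected items do anything for patients. Part of the second measurement comes from an interview with the person in charge of the facility, who by then has been told the first result and the improvements wanted, so a rise may also reflect reporting.

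This would be harmless if preparedness were presented only as a process measure. At stake is the sentence in Statistical Analysis that makes it part of the primary effectiveness outcome. On that wording, a report could claim that CASCADE was effective because preparedness rose, with no difference in survival, disability or QoL.

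**Working it through.** The point is structural, so the main check is to set the statements side by side.

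**1. Is the score tied to the content of the intervention?** Yes, by explicit text. Tailoring ("tailored to each participating facility based on findings from the hospital preparedness assessment and gap analysis"), feedback ("Health care facilities will be informed about their preparedness, management practices, and needed improvements based on preimplementation scores and indicators") and rescoring with the same indicators are all in the CASCADE section. The Discussion (Principal Findings) makes the same link when it says that changes prompted by gaps found at baseline may belong to the intervention exposure. A change that is part of the exposure cannot also be evidence that the exposure worked.

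**2. What status does preparedness have?**

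| Section | Status of preparedness |
|---|---|
| Aim | An aim in its own right, beside survival, disability and QoL |
| CASCADE section, definition of effectiveness | Not included |
| CASCADE section, reuse of indicators | Used to estimate effectiveness |
| Outcome Assessment | An increase is the outcome for hospital preparedness |
| Sample Size | Secondary |
| Statistical Analysis | Within the primary effectiveness outcome |

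The last two rows cannot both stand, and the second row conflicts with the last.

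**3. Does the planned test settle the matter?** Statistical Analysis compares the scores by an independent-samples t test or a Mann-Whitney U test. With six hospitals scored once in each phase, this is 6 v 6. The sidedness is not stated for this test.

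- Observed difference needed for p < 0.05 (t test, 10 degrees of freedom), in SD units = t critical × √(2/6). Two-sided: 2.228 × 0.577 = 1.29 SD. One-sided: 1.812 × 0.577 = 1.05 SD.
- True difference needed for 80% power, two-sided 5%: about 1.8 SD.
- Illustration with assumed baseline scores of 40, 50, 55, 60, 70 and 90 (mean 60.8, SD 17.4). The standard error of the difference is 17.4 × 0.577 = 10.1. A gain of 2 points at every hospital gives t = 2/10.1 = 0.20, p = 0.85. A gain of 10 points gives t = 0.99, p = 0.34.

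The planned test is therefore not easy to pass when hospitals differ widely. That concerns how often a significant rise is found. It does not change what a rise means.

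**4. Does the sample size depend on preparedness?** No. It reproduces from survival alone.

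- Hazard ratio = ln(0.57)/ln(0.42) = 0.648.
- Events (Freedman, two-sided 5%, 90% power) = (1.960 + 1.282)² × (1.648/0.352)² = 230.3, so 231 (stated 232).
- Patients = 2 × 231/(2 − 0.42 − 0.57) = 457.4, so 458 (stated 458).
- With 10% dropout: 458/0.9 = 508.9, so 509 (stated 510).

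Changing the status of preparedness leaves these figures as they are.

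**The case against.** **Preparedness is a legitimate aim.** The Aim section lists it, and measuring it before and after answers that aim. Outcome Assessment calls an increase the outcome for hospital preparedness, in a sentence separate from the patient outcomes. This stands. The measure should be kept and reported; the objection is only to its place in the effectiveness outcome.

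**The score is already protected in part.** It is developed in the preintervention phase, precedes feedback, and is held constant afterwards. Observation and record review are planned beside the interview. This also stands, and item-level scoring rules may sit in the full protocol. Neither point changes what a rise measures.

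**The sentence on reusing the indicators ends with stroke care outcomes.** On a generous reading the indicators only support the comparison of those outcomes. That would ease the CASCADE section but not the sentence in Statistical Analysis.

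Three stronger readings are tempting, and the document does not support them.

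- *A significant result is built in.* A reader might note that six rises out of six give 2 × (1/2)⁶ = 0.031 in a sign or signed-rank test. Those are paired tests, and the protocol plans an unpaired one, for which uniform small gains need not suffice. Nor is any rise assured: the hospitals receive suggestions and training, while the assessment covers infrastructure, equipment and staffing, which need not improve on advice.
- *The scored items are exactly the gaps.* This is not stated. Table 1 describes a general schedule of personnel, infrastructure, guidelines, training and management.
- *The score is the fidelity check.* The text says "Implementation fidelity will be assessed using both facility-level and patient-level indicators" and follows at once with "Preintervention and postintervention hospital preparedness assessments using standardized tools will evaluate changes in infrastructure, service availability, referral mechanisms, and stroke preparedness processes". The link is natural but rests on position, and training attendance, supervision and protocol adherence are also monitored during implementation. The argument here does not need it.

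**Conclusion.** The point holds in this form. A rise in preparedness mainly records uptake, or reported uptake, of the recommendations and is not evidence of patient benefit. Statistical Analysis places it in the primary effectiveness outcome, against Sample Size (secondary) and against the definition of effectiveness in the CASCADE section.

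No numerical bias can be attached to this, because the document gives no expected score, spread or minimum change. The consequence is for the claim: as written, effectiveness could be declared partly on a process measure. The conclusion rests on the explicit sequence of tailoring, feedback and rescoring, and on the three conflicting statements of status. It does not rest on any assumption about how many hospitals will improve. It is confined to the preparedness score; survival, mRS and QoL are separate measurements on patients.

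**What to change.** Reconcile four sections (the CASCADE section, Outcome Assessment, Sample Size and Statistical Analysis) to say the following.

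1. Hospital preparedness is a secondary implementation (process) outcome that answers the preparedness aim. A rise is reported as uptake.
2. Any statement that CASCADE is effective rests on the patient outcomes, with 28-day survival primary.
3. Where possible, postintervention preparedness scores rest on observation and record review, and not on the person-in-charge interview alone.

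The first two are changes of wording that agree with what Sample Size and the definition of effectiveness in the CASCADE section already say. The third uses methods already planned. The sample size and the survival, mRS and QoL analyses do not change. The timing is favourable: by February 2026, 98 of the 255 preintervention patients had been recruited, and feedback to hospitals comes only after the model is developed. The small downside is that preparedness can no longer be presented as a headline effectiveness result.

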**Figure 1 figure1:**
[figure not shown]
Schematic representation of the development and implementation of the Comprehensive Acute Stroke Care Model (CASCADE).

### Data Collection

#### Patient-Related Information

Data collection will be conducted through face-to-face or telephonic interviews with patients who had a stroke or their caregivers (if patients are aphasic). Acute stroke cases will be assessed through an in-person interview at the time of presentation at hospital (recruitment), during the hospital stay, and at discharge. Clinical and laboratory records will be reviewed to collect data on stroke type, clinical presentation, investigations, patient and sample journeys, disability assessment, and treatment outcomes (death, disability, and QoL). Telephonic interviews are planned for follow-ups if travel is not feasible, with medical records sourced via email or other personalized social media platforms. This is being done to improve participant retention in the study.

#### Hospital Preparedness

Observation of facilities, record review, and interviewing the personnel in charge of the health care facility (key informant interviews) will be recorded.

Trained data collectors collect data using a low-literacy, user-friendly digital data collection platform. These data get uploaded into a password-protected (3 layers) server with access only to specific authorized individuals within the study team.

#### Follow-Up

After discharge, all cases will be followed up for a period of 1 year after the stroke at 4 time points (Figure 1): 28 days (for stroke-related deaths), 3 months (for disability), and 6 and 12 months (to assess the process of rehabilitation along with survival, disability, and QoL).

#### Monitoring and Review

The core team will closely supervise data collection with 5% repeat data collection for assessment of completeness, accuracy, and quality of data collected on patients. Any deviation or errors >10% would call for repeat assessment.

An independent monitoring team will oversee project implementation, comprising midlevel specialists from community medicine, neurology, and social work, ensuring adherence to protocol, conducts quarterly monitoring visits, and reports progress and challenges to the study team.

An expert advisory group, including specialists in neurology, neurosurgery, epidemiology, and public health, will provide strategic direction and technical support. They will also provide timely advice to investigators and review the master protocol, suggesting modifications as needed.

#### Training

The training for data collectors will be participatory, using different methods by specialized personnel for each domain. We plan to conduct induction and refresher training at the beginning of each data collection cycle to ensure standardization. To ensure quality apart from rigorous training, weekly and fortnightly review and problem-solving meetings will be held.

### Outcome Assessment

Increased survival, reduced disability, and improvement in stroke-specific QoL after introducing the CASCADE compared to the preintervention phase is considered an outcome. An increase in the scores and indicators of hospital preparedness and management practices is considered as the outcome for hospital preparedness.

### Study Duration

The study will be conducted for 4 years, which comprises of 6 months for development and implementation of the CASCADE and 1 year each for before and after the intervention.

### Statistical Analysis

The respondents in the preimplementation phase of the CASCADE are considered group 1 and those in the postimplementation phase as group 2. The primary outcome for CASCADE effectiveness includes improved hospital preparedness and improved patient treatment outcomes (death, disability, and QoL). The timing and sequence of implementation at each site will be documented in case of minor variations in the timing of intervention implementation across participating sites due to administrative or operational factors beyond the control of the investigators. These factors will be incorporated into the statistical analysis plan. Site-level and time-related variations will be adjusted for during analysis to account for potential differences in implementation timing across hospitals. We hypothesize that the treatment outcomes in group 2 will be better than those in group 1. The Kaplan-Meier method will be used for estimating the survival functions of the two groups at follow-up. The log-rank test will be used to compare the survival distributions between the two groups for each time point. Finally, the Cox proportional hazards regression analysis will be performed at each of the 4 time points separately in which the grouping variable is the intervention (CASCADE) in addition to potential confounders. Relevant patient-level covariates, including stroke severity, National Institutes of Health Stroke Scale score, timing of presentation, referral pathway, and other clinical characteristics, will be considered as potential confounders in adjusted analyses. The QoL before and after the implementation of the CASCADE will be compared using an independent sample 1-tailed *t* test or the Mann-Whitney *U* test depending on the normality assumption. Linear mixed models will be used in which QoL is the dependent variable and the CASCADE is the main independent variable. In the model, the group and the 4 time points are fixed factors and participants are considered as random. The modified Rankin Scale (mRS) scores before and after implementation of the CASCADE will be compared using the Mann-Whitney *U* test at each time point after adjusting for multiple comparisons using the Bonferroni method. Survival rate by different categories of stroke (hemorrhagic and ischemic) and by different severities of stroke (Glasgow Coma Scale and mRS based) will be used for evaluation of effectiveness of the model.

To address the possibility of time-varying confounding in the quasi-experimental study design, the study incorporates collection of several patient-level and system-level variables during both preintervention and postintervention phases. Patient-level variables include stroke severity, National Institutes of Health Stroke Scale score, mRS score, timing of presentation (including arrival within the golden hour), referral pathways, investigations performed, and treatments received. These variables will help assess differences in case mix and care processes across study periods.

In addition, hospital preparedness assessments conducted during both phases will capture system-level and organizational changes, including patient attendance patterns, staffing, infrastructure, referral mechanisms, service availability, and operational changes occurring over time.

These variables will be considered during analysis and interpretation to contextualize observed differences between preintervention and postintervention phases and reduce the impact of time-varying confounding. The objective is to achieve improved survival rate at every level of case severity in proportion to the level of the stroke care facility.

For improved hospital preparedness, the specific scoring system developed and indicator data will be compared using an independent samples *t* test or the Mann-Whitney *U* test depending on normality.

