Pathways to care schedule to collect information on stroke outcome	Includes information related to different treatments and care sought in different places or systems of medicine before reporting to the study hospitals	All patients who report to the hospitals enrolled for assessment of the CASCADE	As and when individuals report to study hospitals with stroke during the study period, preintervention and postintervention of the CASCADE
Outcome schedule	Information related to survival, and disability: Modified Rankin Scale and Stroke-Specific Quality of Life Scale	All patients who report to the hospitals enrolled for assessment of the CASCADE	As and when individuals report to study hospitals with a stroke during the study period and subsequent follow-ups (28 days, 3 months, 6 months, and 12 months after the stroke)
CASCADE schedule	Information related to the standardized CASCADE. This shall contain treatment and management algorithms for stroke care at different levels of health care. This will be developed using information from the preparedness, management, pathways to care, and outcome schedules followed by validation by an expert advisory group. This will be a synthesis of data of all patients who report to the hospitals enrolled for assessment of the CASCADE in the preintervention phase.	All patients who had a stroke within the study hospitals who are eligible for assessment in both the preintervention and postintervention period of the study	As and when individuals report to study hospitals with stroke during the study period preintervention and postintervention of the CASCADE

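### Survival is stratified by an undated mRS, which is also the disability outcome, and benefit is sought at every severity level although the study is sized only for the whole-group comparison

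*Protocol article*

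**What the plan says.** In the Protocol article, Statistical Analysis, the two whole groups are compared by Kaplan-Meier, log-rank and Cox methods. The section adds that survival by stroke type and "by different severities of stroke (Glasgow Coma Scale and mRS based) will be used for evaluation of effectiveness of the model". Further on, it states an aim of "improved survival rate at every level of case severity in proportion to the level of the stroke care facility".

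The mRS has other roles in the same document:

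- **Outcome instrument.** The outcome schedule in Table 1 (Description of Materials) contains "Information related to survival, and disability: Modified Rankin Scale and Stroke-Specific Quality of Life Scale". Its timing is "As and when individuals report to study hospitals with a stroke during the study period and subsequent follow-ups", which are listed as 28 days and 3, 6 and 12 months.
- **Tested outcome.** Statistical Analysis says that mRS scores before and after implementation "will be compared using the Mann-Whitney *U* test at each time point after adjusting for multiple comparisons using the Bonferroni method".
- **Case-mix variable.** The section also says: "Patient-level variables include stroke severity, National Institutes of Health Stroke Scale score, mRS score, timing of presentation", without a date for the mRS.

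NIHSS is named as a potential confounder ("Relevant patient-level covariates, including stroke severity, National Institutes of Health Stroke Scale score, timing of presentation") but is not used to form the strata. Sample Size bases the 510 patients on whole-group 28-day survival alone.

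**The concern.** There are two separate problems.

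**Which mRS forms the strata.** CASCADE is meant to reduce disability. An mRS recorded during the hospital stay, at discharge or at follow-up is therefore partly a product of the intervention. If it works, patients who were sicker at onset move into milder mRS strata in the post-intervention group. Survival within a given mRS stratum then compares unlike patients, and a difference can be hidden or created. A value taken at presentation, before the intervention acts, does not have this fault. The text allows either.

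**What the strata can show.** The objective speaks of every severity level, but the study has the events for one comparison of the two whole groups. Separate stratum survival rates will scatter around a common effect. A reader who judges the model level by level may take that scatter for failure in some strata or special success in others.

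**Working it through.** **Inputs** (Protocol article, Sample Size): survival 42% before and 57% after; hazard ratio 0.65; 5% level; 90% power; 232 events; 458 patients; 10% dropout; 510 enrolled, 255 per group. The sidedness of the test is not stated there; two-sided 5% closely reproduces the plan's figures.

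**1. The plan's own figure.**

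- HR = ln(0.57)/ln(0.42) = 0.648.
- Freedman events: E = (1.960 + 1.282)² × [(1 + HR)/(1 − HR)]² = 10.51 × (1.648/0.352)² ≈ 230.3, rounded up to 231 (stated 232).
- Patients: N = 2E/(2 − 0.42 − 0.57) = 462/1.01 = 457 (stated 458).
- Dropout: 458/0.90 = 509, or 510 for equal groups.

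The plan's figure reproduces. With 510 × 0.90 = 459 evaluable patients, expected events are 459 × (1 − 0.495) = 231.8. Power is Φ(√231.8 × 0.352/1.648 − 1.960) = Φ(1.29) = 90.2%.

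**2. The same formula within k strata.** Assumptions: k equal, independent strata with the same 42% to 57% gain in each, tested at two-sided 5%. Events per stratum are 231.8/k. The chance of the right direction uses z = 0.15/√[(0.42×0.58 + 0.57×0.43)/n], with n = 229.5/k per group.

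| k | Events per stratum | Power per stratum | All significant | All in right direction | At least one false positive if no effect |
|---|---|---|---|---|---|
| 2 | 115.9 | Φ(0.34) = 63% | 0.633² = 40% | 0.989² = 98% | 1 − 0.95² = 9.8% |
| 3 | 77.3 | Φ(−0.08) = 47% | 0.467³ = 10% | 0.970³ = 91% | 1 − 0.95³ = 14.3% |
| 4 | 57.9 | Φ(−0.33) = 37% | 0.369⁴ = 1.9% | 0.948⁴ = 81% | 1 − 0.95⁴ = 18.5% |

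Equal baseline survival across severity levels is unrealistic, so it was varied. With three equal strata at 70%, 42% and 14% baseline survival (mean 42%) and the same hazard ratio, power is 26%, 47% and 65%. All three are then significant with probability 0.264 × 0.467 × 0.651 = 8%, against 10%.

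**3. Direction and size of the mRS bias, as an illustration.** All parameters are assumed; none comes from the protocol. In a simulation of 2,000,000 patients, the intervention lowers a post-onset mRS by 0.3 SD of baseline severity and has no effect on death. Survival, pre versus post:

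| Strata | Mildest third | Middle third | Most severe third |
|---|---|---|---|
| Baseline severity | 75.6 vs 75.7% | 41.6 vs 41.6% | 14.2 vs 14.1% |
| Post-onset mRS | 69.0 vs 65.0% | 42.5 vs 36.8% | 19.9 vs 16.7% |

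Thirds of baseline severity correctly show no difference. Thirds of the post-onset mRS show false harm of about 3 to 6 points. When a true survival benefit is added, the gaps of 12, 20 and 13 points seen by baseline severity shrink to 10, 12 and 10 points by post-onset mRS.

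**The case against.** The strongest reply is that the natural reading is an initial mRS. The text pairs it with the Glasgow Coma Scale under stroke severity, lists it beside NIHSS for case mix, and Table 1 provides a value at presentation. An early value of a scale that later serves as an outcome is a legitimate stratifier, and the exact time point could be set in an analysis plan that is not shown. This stands in part: a reader might infer that the mRS strata are biased as planned, and the protocol does not say that. The bias is conditional. But the article chooses an outcome scale as stratifier and does not date it, and Data Collection provides for assessment during the stay and at discharge as well as on arrival.

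The second reply is that the every-level sentence is an aim, with no test, threshold or all-strata criterion attached. This also stands. A reader might infer that a working model would be declared unsuccessful if one stratum failed; no rule in the protocol would do that. Nor does the clause on facility level promise a severity-by-facility grid of tests, so multiplying strata by facility level has no basis in the text. What remains is that the strata are named as evidence of effectiveness, are not labelled supportive, and cannot carry an every-level statement.

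**Conclusion.** The point holds in a limited form. The stratified survival analysis rests partly on an undated outcome scale, and it is biased if that value comes from after the start of care. Separately, the sample cannot reliably show benefit at every severity level. Even with only two equal strata and a uniform true gain, both reach significance about 40% of the time, and with three strata about 10%. The number, size and baseline survival of the strata are assumptions, because the protocol gives none of them. The size of the mRS bias is illustrative only. The whole-group 28-day comparison, with its 90% power under the plan's assumptions, is not affected. The change is worth making, but it does not threaten the main result.

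**What to change.** 1. Define severity strata by NIHSS and Glasgow Coma Scale at arrival, and say that these are arrival values. Drop mRS as a severity stratifier and keep it as the disability outcome.
2. Replace judgement from separate stratum survival rates by a group-by-severity interaction term in the Cox model and, if wanted, a group-by-facility-level term. Label both exploratory. Show stratum hazard ratios with confidence intervals as description.
3. Reword the every-level objective so that stratum results support the whole-group comparison.

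**Cost.** This is analysis wording. NIHSS is already listed among the variables collected in both phases, and Glasgow Coma Scale is already named as a stratifier; the team should confirm that both are recorded at arrival. Results reports 98 of 255 pre-intervention patients recruited by February 2026, and the Abstract says that analysis follows completion of recruitment, so the change can precede any comparison of outcomes.

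**Downside.** The interaction tests have low power. With two equal strata of 115.9 events, the standard error of the difference in log hazard ratios is about √(4/115.9 + 4/115.9) = 0.263. For 80% power the two hazard ratios would have to differ by a factor of exp(2.80 × 0.263) ≈ 2.1. A non-significant interaction must therefore not be reported as proof of equal benefit.
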